### Data management and quality control

Phase 1 data will be collected using the structured assessment of technical skills (see Fig. 5), the learner evaluation form (see Fig. 6), a learner demographic form (Fig. 7), and a learner feedback form (Fig. 8). These paper forms will then be transcribed into the Research Electronic Data Capture (REDCap) online tool. Phase 2 data will be collected by experienced female nurses who will be employed and trained for the study. Female nurse will be hired due to cultural acceptability, allowing access to the LR/OR. The data collector nurses will operate independently of both the clinical and POCUS teams, and will be available 24 h each day. They will initially collect intubation data using a patient data collection form (Fig. 9), then immediately transcribe the forms into REDCap.

**Fig. 7 Fig7:**
[figure not shown]
Learner Demographic Form

**Fig. 8 Fig8:**
[figure not shown]
Learner feedback form

**Fig. 9 Fig9:**
[figure not shown]
Patient Data Collection Form

For quality control, each POCUS examination will be recorded as a deidentified Mpeg4 video file on the POCUS tablet. These files will be sent via a secure online file transfer program to a non-AKUH paediatric intubation POCUS expert who was not part of study interventions and is blinded to any patient details. The expert will rate each video for high or low quality images, and will record an interpretation of esophageal or tracheal intubation.

### Measurement of outcomes

The primary outcome is diagnostic accuracy [(true positives+ true negatives)/total N] of POCUS (performed by healthcare providers with a brief education in intubation POCUS) for identifying tracheal versus esophageal intubation in newborns. The reference standard will be a composite of standard-of-care methods (auscultation, colorimetric capnography, and chest x-ray). The secondary outcome is the time difference between POCUS and standard-of-care methods in determining ETT location. The tertiary outcomes include the level of agreement between POCUS users and standard-of-care methods, the level of agreement between POCUS users and a POCUS expert, and the level of agreement between the POCUS expert and standard-of-care methods.

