### Hypotheses

Neonatal health care providers trained on a novel ultrasound simulator in ETT localization will be > 95% accurate, compared to an external POCUS expert, when performing POCUS on intubated neonates, and will produce a result in less time than the current standard-of-care methods for ETT localization.

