### Sample size

Phase 1 will involve 60 healthcare providers who attend deliveries and are exclusively involved in newborn care, which include 6 neonatal attending physicians, 8 neonatal fellows, 38 postgraduate medical trainees, and 8 senior nursing staff. These providers are all skilled in standard-of-care methods for ETT confirmation. Each 2-hour training session involves 15 participants, and the sessions are conducted 4 times.

The phase 2 sample size calculation indicates that a total of 292 neonatal intubations are required. There are approximately 5000 deliveries per year at AKUH, of which approximately 12% (600) of these newborns are admitted to the NICU. Approximately 70% (420) of these patients require intubation in a given year. The rates of incorrect esophageal intubation reported in the most recent multi-center study ranged from 1 to 12% [13]. Using a conservative rate of 5%, the sample size was calculated for the primary outcome (accuracy) using a two-sided equivalence test for correlated proportions. The standard proportion of correct tracheal intubation was assumed to be 95% and the maximum allowable difference between POCUS and standard-of-care methods was set to 0.05 (*α)*. To achieve 80% power at a 5% significance level, a total of 222 participants are needed for the primary outcome.

For the secondary outcome (time difference between POCUS and standard-of-care methods), using a conservative time difference of 5 s, we estimate a total sample size of 252 newborns will be needed to achieve a two-sided alpha of 0.05 and power of 80%.

Sample size estimates for the tertiary outcome are based on the kappa (κ) statistic for measuring agreement between POCUS and standard-of-care methods. Assuming 95% true agreement and a kappa statistic of 0.90, a sample size of 292 subjects results in a two-sided 95% confidence interval with a width of 0.100 (i.e. k = 0.85–0.95) using the Cohen’s large-sample formula for standard deviation of κ.

Therefore, to achieve all study objectives, a minimum sample size of *n* = 292 will be targeted.

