### Data processing and analysis

Key study variables will be summarized univariately using means/standard deviations/histograms and frequencies/proportions as appropriate.

We will calculate sensitivity, specificity, positive and negative predictive values, positive and negative likelihood ratios, and the κ statistic (all with 95% confidence intervals) using standard formulas for a binomial proportion.

The mean time difference between POCUS and standard-of-care methods will be analyzed using paired sample t-tests. If the time distribution is skewed, we will examine median time differences using Wilcoxon signed-rank tests for matched data.

Data analysis will use SPSS statistical software, with the type 1 error rate set to 0.05. A subgroup analysis of premature newborns status will be performed as sample size permits. We will also analyze user accuracy as a function of number of POCUS exams performed during the study. An ad-hoc power analysis will be performed on stratified effects at study completion.

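### Overall accuracy with a >95% hypothesis says little about detecting esophageal tubes when the plan assumes that 95% of tubes are tracheal

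*Protocol article*

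**What the plan says.** Measurement of outcomes in the protocol article fixes the primary measure: "The primary outcome is diagnostic accuracy [(true positives+ true negatives)/total N] of POCUS". The comparator there is the usual bedside and imaging checks taken together: "The reference standard will be a composite of standard-of-care methods (auscultation, colorimetric capnography, and chest x-ray".

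Hypotheses sets the benchmark, but against a different comparator. Trained providers "will be > 95% accurate, compared to an external POCUS expert".

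Sample size takes 5% as the esophageal rate and 95% as the proportion tracheal. It gives the published background as "The rates of incorrect esophageal intubation reported in the most recent multi-center study ranged from 1 to 12" percent. It arrives at 222 intubations for accuracy, from an equivalence test on paired proportions with a margin of 0.05, and at an overall target of 292.

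Data processing and analysis adds the other accuracy measures: "We will calculate sensitivity, specificity, positive and negative predictive values", together with likelihood ratios and kappa, all with 95% intervals. None of these is primary or has a target. Kappa is the only one used in a sample size calculation.

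**The concern.** The article's Background presents neck ultrasound mainly as a way to recognise a tube in the esophagus quickly, because an unrecognised one deprives the newborn of oxygen. Overall accuracy gives every tube the same weight. When 95 tubes in 100 are tracheal, about 95% of the score comes from tubes for which this question does not arise. The hypothesised 95% is also the score expected from calling every tube tracheal.

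The trial could therefore report a favourable primary result although POCUS had missed a large share of the esophageal tubes. A reader who looked only at the primary outcome would not know.

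**Working it through.** **Inputs.** Esophageal rate p = 0.05, with a cited range of 0.01 to 0.12, and N = 292 (Sample size). Benchmark 0.95 (Hypotheses). Accuracy = (TP + TN)/N (Measurement of outcomes). Below, positive means esophageal, Se is the share of esophageal tubes detected, and Sp is the share of tracheal tubes called tracheal.

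**The plan's own figure.** The 222 for accuracy can be neither confirmed nor refuted, because the discordant proportion is not given. Under the usual formula n = (z_alpha + z_beta)² × pd / 0.05², 222 corresponds to pd between about 0.053 and 0.090, depending on the alpha and beta convention. Nothing below depends on it.

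**Expected accuracy** = p × Se + (1 − p) × Sp.

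- All called tracheal, p = 0.05: 0.05 × 0 + 0.95 × 1 = 95.0%.
- Same reader at p = 0.01: 99%. At p = 0.12: 88%.
- Half of esophageal tubes missed, Sp = 1, p = 0.05: 0.05 × 0.5 + 0.95 × 1 = 97.5%.

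**Two possible readings of more than 95%.** The article states neither as a rule, so both are tried.

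- Point estimate above 95%: at most 14 errors in 292 (278/292 = 95.2%; 277/292 = 94.9%).
- Lower exact (Clopper-Pearson) 95% limit above 95%: at most 7 errors (lower limit 95.1% with 7 errors, 94.7% with 8).

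With Sp = 1 the number of errors is binomial with size 292 and probability p × (1 − Se). The chance of meeting each reading is:

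| Reader | p | Observed accuracy > 95% | Lower limit > 95% |
|---|---|---|---|
| Misses half | 5% | 0.99 | 0.55 |
| Detects none | 2% | >0.99 | 0.77 |
| Detects none | 3% | 0.97 | 0.35 |
| Detects none | 5% | 0.51 | 0.02 |
| Detects none | 8% | 0.02 | <0.001 |
| Detects none | 12% | <0.001 | <0.001 |

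A third reading is a simple Wald equivalence test on the proportion called tracheal, with the 0.05 margin. The reader who detects none passes about 8% of the time at p = 5% and about 93% at p = 2%.

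**Precision for sensitivity.** Expected esophageal tubes: 292 × 0.05 = 14.6. Exact 95% intervals: 15/15 detected gives 78% to 100%; 14/15 gives 68% to 99.8%.

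**The case against.** The strongest reply is that the failure would not stay hidden. Sensitivity, specificity, predictive values, likelihood ratios and kappa are all planned with intervals, and a reader who calls every tube tracheal has kappa 0. This stands. The weakness lies in what the primary result conveys, not in what the study reports as a whole.

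A reader might infer that the primary claim cannot tell a useful detector from a useless one. The article does not support that. It gives no decision rule for the 95% claim, and at its own 5% rate a wholly uninformative reader passes about half the time on the point estimate and about 2% of the time on the confidence limit. At 8% or 12%, both within the cited range, such a reader almost never passes. Higher rates are plausible here: fellows or residents intubate, only the first attempt is scanned, and the Background says that esophageal placement is more frequent with junior trainees. What remains is the partly useful reader. Missing half of the esophageal tubes at a 5% rate, it still passes the stricter confidence-limit rule in more than half of trials.

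A reader might also infer that describing 5% as conservative is a mistake. That is not established. A lowish rate is cautious for the number of esophageal tubes expected, and 5% is a harder accuracy hurdle than 1%. The article does not say which quantity it had in mind.

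The 95% hypothesis is worded against an external expert, whereas the primary outcome uses the standard-of-care composite, so joining the two is an interpretation. The arithmetic holds for either comparator if it labels about 5% of tubes esophageal.

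Finally, the Background also worries about needless re-intubation of correctly placed tubes. That is a reason for specificity to stand beside sensitivity, not for pooling the two.

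**Conclusion.** The point holds in this limited form: the chosen primary measure, read against its 95% benchmark, says little about detection of esophageal tubes. At the plan's 5% rate the benchmark equals the expected accuracy of a reader who finds none of them. POCUS missing half would pass in about 99% of trials on observed accuracy and in about 55% on the exact lower limit.

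These figures assume n = 292, independent tubes and perfect specificity. The two pass rules are constructions, since the article states none. The result for a reader who detects nothing depends strongly on the esophageal rate and should not be quoted without it.

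**What to change.** - Define positive as esophageal.
- Make sensitivity for esophageal placement and specificity co-primary, each with an exact 95% interval.
- Keep overall accuracy as a secondary measure, shown beside the observed proportion tracheal.
- Reword the 95% hypothesis to match, and reconcile its comparator (external POCUS expert) with the primary reference standard (standard-of-care composite).
- State the precision to expect for sensitivity: about 15 esophageal tubes at a 5% rate, with 15/15 giving 78% to 100% and 14/15 giving 68% to 99.8%. Note that the 222 was sized for accuracy, not for sensitivity.

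No new data are needed, because sensitivity and specificity are already to be calculated. The cost is an amendment to the outcome and hypothesis wording, and a stated precision for sensitivity that looks less favourable than the present accuracy claim.

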### Hypotheses

Neonatal health care providers trained on a novel ultrasound simulator in ETT localization will be > 95% accurate, compared to an external POCUS expert, when performing POCUS on intubated neonates, and will produce a result in less time than the current standard-of-care methods for ETT localization.

### Sample size

Phase 1 will involve 60 healthcare providers who attend deliveries and are exclusively involved in newborn care, which include 6 neonatal attending physicians, 8 neonatal fellows, 38 postgraduate medical trainees, and 8 senior nursing staff. These providers are all skilled in standard-of-care methods for ETT confirmation. Each 2-hour training session involves 15 participants, and the sessions are conducted 4 times.

The phase 2 sample size calculation indicates that a total of 292 neonatal intubations are required. There are approximately 5000 deliveries per year at AKUH, of which approximately 12% (600) of these newborns are admitted to the NICU. Approximately 70% (420) of these patients require intubation in a given year. The rates of incorrect esophageal intubation reported in the most recent multi-center study ranged from 1 to 12% [13]. Using a conservative rate of 5%, the sample size was calculated for the primary outcome (accuracy) using a two-sided equivalence test for correlated proportions. The standard proportion of correct tracheal intubation was assumed to be 95% and the maximum allowable difference between POCUS and standard-of-care methods was set to 0.05 (*α)*. To achieve 80% power at a 5% significance level, a total of 222 participants are needed for the primary outcome.

For the secondary outcome (time difference between POCUS and standard-of-care methods), using a conservative time difference of 5 s, we estimate a total sample size of 252 newborns will be needed to achieve a two-sided alpha of 0.05 and power of 80%.

Sample size estimates for the tertiary outcome are based on the kappa (κ) statistic for measuring agreement between POCUS and standard-of-care methods. Assuming 95% true agreement and a kappa statistic of 0.90, a sample size of 292 subjects results in a two-sided 95% confidence interval with a width of 0.100 (i.e. k = 0.85–0.95) using the Cohen’s large-sample formula for standard deviation of κ.

Therefore, to achieve all study objectives, a minimum sample size of *n* = 292 will be targeted.

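### The 80% power stated for 222 intubations belongs to an equivalence test of how often each method says tracheal, not to the primary outcome (accuracy) or the hypothesis of more than 95%

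*Protocol article*

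**What the plan says.** Four sections of the protocol article bear on this.

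- **Measurement of outcomes.** The primary outcome is accuracy: true positives plus true negatives over the total. The reference standard is the composite of auscultation, colorimetric capnography and chest x-ray.
- **Hypotheses.** Trained providers will be more than 95% "accurate, compared to an external POCUS expert, when performing POCUS on intubated neonates". The comparator here is the expert, not the composite.
- **Sample size.** The primary outcome is sized "using a two-sided equivalence test for correlated proportions". The inputs are "Using a conservative rate of 5"% for esophageal intubation and "The standard proportion of correct tracheal intubation was assumed to be 95"%. The margin is given as "the maximum allowable difference between POCUS and standard-of-care methods was set to 0.05", with the symbol alpha beside it. The result: "To achieve 80% power at a 5% significance level, a total of 222 participants are needed for the primary outcome". The final target is 292, which comes from the kappa calculation.
- **Data processing and analysis.** "We will calculate sensitivity, specificity, positive and negative predictive values", likelihood ratios and kappa, all with 95% confidence intervals.

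**The concern.** A sample size calculation supports a power claim only for the quantity it tests. Standard of care is the reference standard, so its accuracy is 100% by definition. The 95% assigned to it can therefore only be the share of tubes that are tracheal, and the paired comparison is between two marginal shares, not two accuracies.

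In such a comparison a missed esophageal tube and a false esophageal call cancel; in accuracy they add up. POCUS could match the composite's share of tracheal calls while being wrong about many individual tubes. Missed esophageal tubes are the error the study is meant to address, so a reader who takes the stated 80% as power for accuracy would be misled.

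**Working it through.** **Notation.** Positive means tracheal. FP is the proportion of all tubes that are esophageal but called tracheal; FN is the proportion that are tracheal but called esophageal.

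- Difference tested by the equivalence calculation: (TP + FP) − (TP + FN) = FP − FN.
- Primary outcome: accuracy = 1 − (FP + FN).

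With both marginal shares at 95%, FP = FN and each can lie anywhere from 0 to 0.05. The tested difference is then 0 for every accuracy from 90% to 100%. POCUS calls unrelated to the truth would give 0.95² + 0.05² = 90.5% accuracy and a difference of 0.

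**Reproducing 222.** Inputs from Sample size: margin 0.05, 5% significance, 80% power. A paired test also needs a discordant proportion, which is not stated for this calculation. I assume 5%, because the kappa paragraph of the same section works from "Assuming 95% true agreement and a kappa statistic of 0.90". With true difference 0, FP = FN = 0.025. Using two one-sided tests at 0.05 and the score variance restricted to the null:

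- Restricted null estimates: 0.0149 and 0.0649, so s0 = √(0.0149 + 0.0649 − 0.05²) = 0.278.
- Under the alternative: s1 = √0.05 = 0.2236.
- N = [(1.645 × 0.278 + 1.282 × 0.2236) / 0.05]² = 221.3, rounded up to 222.

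The match depends on the formula. A Wald variance at 5% discordance gives 172 (0.05 in each tail) or 211 (0.025 in each tail).

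**What that assumption implies.** Accuracy = 1 − 0.05 = 95%, the null value of the hypothesis if the 95% benchmark is applied to the standard-of-care reference. POCUS would miss 0.025 / 0.05 = half of the esophageal tubes. The chance of showing accuracy above 95% is then only the type I error of an exact test with upper tail 0.025: 1.2% at 222 and 2.0% at 292.

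**A poor reader under the equivalence criterion.** Suppose POCUS detects no esophageal tube and calls 5% of tracheal tubes esophageal, at a 5% esophageal rate. Then FP = 0.05, FN = 0.95 × 0.05 = 0.0475, the difference is 0.0025 and accuracy is 1 − 0.0975 = 90.25%. Probability of being declared equivalent (Wald limits, margin 0.05):

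| Limits | n = 222 | n = 292 |
|---|---|---|
| 90% | about 54% | 72% |
| 95% | 34% | 56% |

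**Power for accuracy above 95%.** Exact binomial test. The article gives no expected true accuracy, so a range is shown.

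| n | Upper tail | Correct calls needed | 97% | 98% | 98.5% | 99% |
|---|---|---|---|---|---|---|
| 222 | 0.025 | 218 | 20% | 54% | 76% | 93% |
| 222 | 0.05 | 217 | 34% | 71% | 88% | 97.5% |
| 292 | 0.025 | 285 | 35% | 77% | 92% | 99% |
| 292 | 0.05 | 284 | 49% | 87% | 97% | 99.7% |

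**Precision instead of a test.** Half-width at 95% accuracy: 1.96 × √(0.95 × 0.05 / 292) = 2.5 percentage points; at 222 it is 2.9.

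**The case against.** Several points on the other side stand.

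- **The arithmetic of 222 is not shown to be wrong.** It reproduces under an assumption that agrees with the kappa paragraph. A reader using a Wald formula might infer a larger discordance and a design accuracy below 95%, but that depends on the formula and the article does not support it.
- **The trial enrols 292, not 222.** A reader might infer that the study is underpowered. That does not follow: at 292 power is 87% at true accuracy 98% with a one-sided 0.05 test, and 92% at 98.5% with the stricter tail. It is low only if true accuracy is near 97% or below.
- **A reader might infer that the plan lacks a primary test.** The article condenses a fuller plan, and a formal test may be in an analysis plan that is not shown. The point does not need that absence: the outcome, hypothesis and sample size sections conflict within the article, and adding the equivalence test to another document would leave it testing a different quantity.
- **The poor-reader example is constructed.** Its misses and false alarms nearly balance, and the planned sensitivity and specificity would expose it. It shows what the criterion permits, not what is likely to be reported.
- **Accuracy has a weakness of its own.** A reader who always says tracheal has accuracy of 1 minus the esophageal rate. The article cites rates from 1 to 12%. At 292, that reader would pass the exact test against 95% (upper tail 0.025) in 99% of trials at a 1% rate and 77% at 2%. An accuracy test alone is not a complete remedy.

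The alpha beside the margin is a notation slip.

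**Conclusion.** The concern holds as a mismatch between the calculation and the question. The 80% power attached to 222 is power to show that two marginal shares differ by less than 0.05. It is not power for accuracy as defined under Measurement of outcomes, nor for the claim of more than 95% under Hypotheses, which also uses a different comparator. At the discordance that reproduces 222, accuracy equals the benchmark and could be shown to exceed it only by chance.

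This rests on two assumptions: that the 5% discordance, not stated for this calculation, is the one used, and that the 95% benchmark is carried over from the expert to the standard-of-care reference. The algebraic mismatch between FP − FN and FP + FN needs neither.

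This should be fixed, but it does not threaten the trial: the target of 292 was set by kappa, no extra patients are needed, and the planned intervals for sensitivity and specificity protect the conclusions.

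**What to change.** Keep n = 292 and replace the equivalence calculation with one of the following:

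1. an exact binomial lower limit for accuracy against 95%, with the power at 292 stated over a range of true accuracies, as in the table above, and the tail probability named; or
2. a precision statement, about ±2.5 percentage points at 95% accuracy, which suits the interval-based analysis already described.

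Then:

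- Make Measurement of outcomes and Hypotheses use one comparator for the primary claim. Agreement with the other can stay among the tertiary outcomes.
- State that accuracy will be read together with sensitivity and specificity and their intervals, because always calling tracheal scores well when esophageal tubes are rare.
- Remove the alpha label from the 0.05 margin if the margin is mentioned at all.

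The cost is rewording of the outcome, hypothesis and sample size text. The power statement becomes less favourable if true accuracy is below about 98%. No change to enrolment or data collection is needed.

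### The target of 292 rests on a kappa calculation that implies a roughly 50/50 tracheal/esophageal split, against the plan's own 5% esophageal rate, so the stated interval width of 0.100 is not delivered

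*Protocol article*

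**What the plan says.** The Sample size section of the protocol article makes three calculations for phase 2.

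- **Primary outcome (accuracy).** The source cited for esophageal intubation gives a range: "The rates of incorrect esophageal intubation reported in the most recent multi-center study ranged from 1 to 12" percent. From this the plan takes one value: "Using a conservative rate of 5%, the sample size was calculated for the primary outcome (accuracy"). The matching tracheal proportion is set at 95%. The result is that "a total of 222 participants are needed for the primary outcome".
- **Secondary outcome (time difference).** 252 newborns.
- **Tertiary outcome (how well POCUS agrees with the standard of care, measured by kappa).** The text reads: "Assuming 95% true agreement and a kappa statistic of 0.90, a sample size of 292 subjects results in a two-sided 95% confidence interval". That interval is said to run from 0.85 to 0.95, a width of 0.100, and the method named is Cohen's large-sample standard deviation.

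The section then takes the largest of the three: "Therefore, to achieve all study objectives, a minimum sample size of" 292 is the target. The chance agreement, or the tracheal/esophageal split, behind the kappa calculation is not stated.

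**The concern.** Kappa corrects observed agreement for the agreement expected by chance, and chance agreement depends on how often each method calls a tube esophageal. Once agreement and kappa are both fixed, chance agreement is fixed too, and so, nearly, is the split between the categories. The pair chosen here (95% and 0.90) fits a population with about equal numbers of tracheal and esophageal tubes. The rest of the section describes a population with 95% tracheal tubes.

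Two things are at stake. First, 292 exceeds 222 and 252 only because of this calculation, and the section says that it serves every objective. For the agreement objective, the promised precision is not there. Second, the protocol commits to reporting kappa with a 95% confidence interval. If POCUS reaches exactly the planned 95% agreement at a 5% esophageal rate, kappa will come out near 0.5. Set beside a planned 0.90 (0.85 to 0.95), that result could be taken for a failure of the technique when it is a consequence of prevalence.

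**Working it through.** **Inputs, all from the Sample size section:** observed agreement Po = 0.95; kappa = 0.90; n = 292; two-sided 95% interval (z = 1.96); stated width 0.100; planned esophageal rate 5%; cited range 1% to 12%.

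**Formulas**

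- kappa = (Po − Pe)/(1 − Pe), so Pe = (Po − kappa)/(1 − kappa)
- Cohen's large-sample SE = √[Po(1 − Po) / (n(1 − Pe)²)]; width = 2 × 1.96 × SE
- If the two methods call proportions p and q esophageal, Pe = pq + (1 − p)(1 − q)

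**Step 1: reproduce the plan's figure**

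- Pe = (0.95 − 0.90)/(1 − 0.90) = 0.50
- SE = √[0.95 × 0.05 / (292 × 0.50²)] = 0.0255; width = 0.09999
- Solving for a width of 0.100 gives n = 292

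The published figure reproduces exactly, so Pe = 0.50 is what the calculation used.

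**Step 2: what Pe = 0.50 means**

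Pe = 0.50 requires (2p − 1)(2q − 1) = 0, so at least one method calls exactly half the tubes esophageal. With 95% agreement the other method can differ by at most 5 percentage points, so it lies between 45% and 55%.

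**Step 3: repeat at the planned 5% rate, both methods at 5%**

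Pe = 0.95² + 0.05² = 0.905, so 1 − Pe = 0.095.

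- *Keep kappa 0.90.* Po = 0.905 + 0.90 × 0.095 = 0.9905. SE = √[0.9905 × 0.0095 / (292 × 0.095²)] = 0.0598; width = 0.234. A width of 0.100 would need n = 1,603.
- *Keep 95% agreement.* kappa = (0.95 − 0.905)/0.095 = 0.474. SE = √[0.95 × 0.05 / (292 × 0.095²)] = 0.134; width = 0.526. A width of 0.100 would need n = 8,088.

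**Step 4: across the cited range, n = 292, both methods at the same rate**

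| Esophageal rate | Pe | Po needed for kappa 0.90 | Width at kappa 0.90 | Kappa at Po = 0.95 | Width at Po = 0.95 |
|---|---|---|---|---|---|
| 1% | 0.980 | 0.998 | 0.515 | not attainable | not applicable |
| 5% | 0.905 | 0.9905 | 0.234 | 0.474 | 0.526 |
| 12% | 0.789 | 0.979 | 0.156 | 0.763 | 0.237 |
| 50% (implied) | 0.500 | 0.950 | 0.100 | 0.900 | 0.100 |

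At 1% in both methods, at most 2% of tubes can be discordant, so agreement cannot be as low as 95%.

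**Step 5: does the choice of formula or the equal-rates assumption matter?**

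- The full asymptotic (Fleiss-Cohen-Everitt) standard error at 5% gives a width of 0.233 at kappa 0.90 and 0.460 at 95% agreement.
- A simulation of 20,000 samples of 292 at 5% and kappa 0.90 puts the central 95% of estimates between about 0.75 and 1.00.
- With one method at 5%, the other between 0% and 10%, and 95% agreement, kappa runs from 0 to 0.64 and the width from 1.0 down to 0.36.

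The common cause is the small number of esophageal tubes: 292 × 0.05 = 14.6 expected.

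**The case against.** The strongest reply is that little depends on this. Kappa belongs to a tertiary outcome, no hypothesis or decision rule uses it, and 292 is above the stated needs for the primary and secondary outcomes. The effect on size is 292 − 252 = 40 extra newborns, which does those outcomes no harm. This limits the consequence, but the stated width is still wrong, and it is the sole stated reason for 292.

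Some points on wording are fair:

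- The arithmetic is correct for its inputs. The fault is that the inputs are incompatible with the planned rate. The even split is implied by them, not written down.
- The width of 0.100 is out of reach under the stated inputs, but not in every conceivable case. At 5%, a true kappa of 0.98 would give about 0.105. That corresponds to 0.55 expected disagreements in 292, where the large-sample formula cannot be trusted.
- The replacement figures are approximate too. At kappa 0.90 and 5%, only about 2.8 disagreements are expected, and the symmetric interval (0.783 to 1.017) passes the maximum of 1. The kappa of 0.47 assumes that both methods call 5% esophageal.
- The protocol sets no kappa threshold, so a misreading of a low kappa is a risk and not a certainty. For POCUS against the standard-of-care composite, positive and negative percent agreement are the same numbers as the sensitivity and specificity already planned.

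None of this restores the stated interval.

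**Conclusion.** The concern holds. The stated pair of 95% agreement and kappa 0.90 contradicts the 5% esophageal rate in the same section. With 292 newborns at that rate, the 95% interval for kappa is about 0.23 wide if kappa is 0.90, or about 0.46 to 0.53 wide (depending on the standard error) around a kappa of 0.47 if agreement is 95%. Neither is 0.100, and 0.100 is not reached under either input anywhere in the cited 1% to 12% range. The figures assume equal esophageal rates in the two methods and large-sample standard errors; the checks on both assumptions leave the conclusion unchanged. The damage is confined to the precision claimed for the tertiary agreement outcome and to the statement that 292 meets every objective. The figures of 222 and 252 do not use this calculation.

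**What to change.** Keep n = 292 and correct the text of the Sample size section:

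1. Withdraw the claim of a 0.100-wide interval from 0.85 to 0.95. Replace it with wording such as: *At a 5% esophageal rate by both methods, kappa 0.90 corresponds to about 99% agreement, and 292 newborns give a 95% confidence interval about 0.23 wide (roughly 0.78 to 1.0, upper limit capped at 1). At 95% agreement, kappa would be about 0.47, with an interval about 0.5 wide.* State that both figures are large-sample approximations.
2. Reword the closing sentence. 292 exceeds the stated needs of the primary and secondary outcomes (222 and 252), and the precision for kappa is whatever that number provides.
3. Say in advance that kappa depends strongly on prevalence at 5%, and report positive and negative percent agreement beside each kappa. For POCUS users against standard of care, the planned sensitivity and specificity already supply them; the addition matters for the two comparisons that involve the POCUS expert.

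The cost is wording only, and a less favourable stated precision. It needs no additional newborns and leaves the primary analysis unchanged.
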